1&2	HIV-RNA quantification						X		X
1&2	MPXV quantification (sPCR) + infectivity assessment (cell culture)	X	X	X	X	X	X	X	X
1&2	MPXV sequencing	X	X	X	X	X	X	X	X
1&2	Humoral immune response characterisation (anti- MPXV antibodies quantification, seroneutralization)						X		
1&2 &3	Cellular immune response characterisation						X		
1&2	Genetic host factors determination + auto-immune antibodies detection						X		
1&2	Tecovirimat pharmacokinetics						X		

HIV, human immunodeficiency virus; MPXV, mpox virus.

Please refer to ‘Additional File 2: Appendix F’ in
*Extended data* for further information on sample processing, analysis and storage in the UK
^
7
^.

**
*Participant self-assessment survey.*
** All participants are asked to complete a self-assessment survey from the point of entry into the study until D180
*via* a secure online questionnaire. The questionnaire, completed
*via* online REDCap survey, captures information about the participant’s signs and symptoms, including lesion status.

For Tier 2 and Tier 3 in France, the baseline self-assessment survey includes an additional social and sexual behaviour questionnaire.

**
*Outcome assessment.*
** During the medical assessment on D14, 28, 60 and 180, the clinical status according to a four-point ordinal scale (see the
*Outcomes* section) is recorded.

For participants who are pregnant at any time during the study, they are followed in the study until their pregnancy outcome is known.

*Note:* As participants can consent to enrol in the study at any point after receipt of a positive PCR result for mpox infection, the eCRF can be completed using existing medical notes and results of samples already taken.

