## Data management

### Source data

Source documents serve as the initial records of data and are used to obtain participants' data for the electronic case report form (eCRF). These source documents encompass a variety of materials such as hospital records (including medical history and medication details summarized into the eCRF), clinical and office charts, laboratory and pharmacy records, diaries, microfiches, radiographs, and correspondence. If the eCRF is the sole place where data is originally recorded without any other written or electronic records, the entries in the eCRF are considered source data.

In this study, primary data collection occurs through two main methods:

(i) Study staff at participating sites complete electronic case report forms on enrolment, during scheduled study visits, daily for in-patients, and whenever laboratory results become available.

(ii) Participants complete an online questionnaire daily during the first 14 days of the study (or while they are in the hospital) and at specific time points (D21, D28, D60, and D180).

The data entered in the electronic case report forms and the online questionnaire are stored in separate REDCap databases.

To ensure data quality, automatic data checks are programmed into the REDCap systems, alerting users during data entry to minimize missing, inconsistent, or erroneous data. Study sites are responsible for reviewing the data entered into the case report forms for their respective participants.

Centralized monitoring of all data collected in the study is conducted by the University of Oxford. This monitoring involves evaluating data compliance with the study protocol and assessing accuracy, as outlined in the study-specific Monitoring Plan. When issues are identified, queries are triggered to be resolved by the respective sites. If any issues are detected in the Participant Self-Assessment data, the study site is notified to communicate with the participant if necessary.

On-site monitoring may be necessary if serious or repeated non-compliance with the protocol is identified through centralized monitoring. Local or regional coordinating centers will carry out this on-site monitoring.

The REDCap database is hosted at the University of Oxford for a minimum of 25 years following completion of the study.

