### Statistical method

**
*Analysis population.*
** All eligible participants will be included in the final analysis,
*i.e.*, the final analysis set will be the overall population of enrolled participants (prospective and retrospective, with positive mpox PCR).

**
*Method to account for missing, unused or invalid data.*
** The number, timing and pattern for missing values will be detailed for each outcome measure. For missing primary time-to-event outcome:

The patients who are lost to follow-up or withdrew from the trial and who did not experience the event will be censored at their lost to follow-up or withdrawal datePatients who died before experiencing the event will be censored at day 14If the patient is hospitalized, the event will be censored at hospital discharge day, whereas if the patient is an outpatient, the event will be censored at the last available date in the medical assessment formsIf the outcome is still missing, it will be searched in the Patient Self-Assessment Surveys (PSA)

For the four-point clinical scales at day 14 and day 28, missing data will be imputed by using the last observation carried forward (LOCF) method for “Death” and “All lesions are completely resolved and no serious complications” modalities. Missing outcomes will be searched as done for the primary endpoint.

Endpoints still missing after these recovery steps will remain missing in the analyses.

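### At D28, a resolved rating carried forward from D14 pre-empts the search of surveys and SAE records that could contradict it

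*Protocol article*

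**What the plan says.** The four-level clinical status at D14 and D28 is a secondary outcome rated by a physician or study nurse (Protocol article, Outcomes). Its timing is given under Data collection methods, Outcome assessment: "During the medical assessment on D14, 28, 60 and 180, the clinical status according to a four-point ordinal scale" is recorded. No rating on this scale is scheduled before D14.

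The missing-data rules under Statistical method say that for this scale "missing data will be imputed by using the last observation carried forward (LOCF) method". This applies to two levels only: death, and "All lesions are completely resolved and no serious complications". Active lesions and serious complication/hospitalisation are not carried. The next sentence reads "Missing outcomes will be searched as done for the primary endpoint". In the primary-endpoint rules just above it, the survey comes last and is opened only when the outcome has not been found by then. The paragraph closes: "Endpoints still missing after these recovery steps will remain missing in the analyses".

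The survey captures "signs and symptoms, including lesion status" (Data collection methods). It is completed daily for the first 14 days and then "at specific time points (D21, D28, D60, and D180" (Source data). AEs and SAEs are recorded in the eCRF up to D28 (Harms). Recrudescence or relapse, assessed at D60 and D180, is itself a secondary outcome (Outcomes).

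**The concern.** Carrying death forward is safe because death is absorbing. Resolution is not: the protocol plans to look for recrudescence, and it collects lesion status at D21 and D28. If the carried value is assigned before recorded information is searched, an assumption about D28 displaces evidence about D28. The carried level also asserts that there is no serious complication, and nothing in the rule checks this against SAE records running to D28.

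Among survivors, the only level carried is the most favourable one, so any error in the D28 proportion resolved is an overstatement. The same values enter the proportional odds model planned for the scale. Few participants received an antiviral (55 tecovirimat, 7 cidofovir, 2 both; 64 in all), so a handful of misclassified values could count there.

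**Working it through.** **1. Tracing one participant.** Rated resolved at D14, no D28 rating, D28 survey reports active lesions.
- Carry-forward step: the last observation is resolved, which is an eligible level, so D28 is set to resolved.
- Search step: it applies to missing outcomes, and D28 is no longer missing, so the survey is not opened.
- Residual step: not reached.

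If the search came first, the survey would be opened and D28 would be recorded as active lesions.

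**2. Size at D28.** The document states no missingness or recrudescence figure, so there is nothing to reproduce. All four inputs are assumptions:
- m, share of D28 ratings missing: 10-40%
- p, share resolved at D14: 60-80%
- r, share of those with active lesions again, as a survey would show: 1-10%
- s, share of participants with a missing rating who have a usable survey: 50-100%

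Missingness is taken as unrelated to D14 status and to recrudescence, and the D14 rating as complete. Serious complications found only in SAE records are not counted.

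Overstatement (carry-forward first minus survey first) = m·p·r·s / [(1 - m) + m·p + m·(1 - p)·s]. The denominator is the share of participants with a D28 value after recovery, the same under both orders.

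- Low: 0.1 × 0.6 × 0.01 × 0.5 = 0.0003; denominator 0.90 + 0.06 + 0.02 = 0.98; result 0.03 percentage points. With 601 enrolled, 601 × 0.0003 = 0.2 participants.
- Middle (m 20%, p 80%, r 5%, s 100%): 0.008 / 1 = 0.8 points; 601 × 0.008 = 4.8 participants.
- High: 0.4 × 0.8 × 0.10 × 1 = 0.032; denominator 1; result 3.2 points. 601 × 0.032 = 19.2 participants.

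**3. Direction for the treatment comparison.** Further assumptions: 25% of those unresolved at D14 are still active at D28; recrudescence is 3% untreated and 8% treated; 30% of D28 ratings are missing, all with a usable survey. Share with active lesions = (1 - p) × 0.25 + p × r. Carry-forward first multiplies r by 0.70.

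| D14 resolution | Order | Treated | Untreated | Odds ratio |
|---|---|---|---|---|
| 70% in both | survey first | 0.075 + 0.056 = 0.131 | 0.075 + 0.021 = 0.096 | 1.42 |
| 70% in both | carry first | 0.075 + 0.0392 = 0.1142 | 0.075 + 0.0147 = 0.0897 | 1.31 |
| 80% treated, 60% untreated | survey first | 0.05 + 0.064 = 0.114 | 0.10 + 0.018 = 0.118 | 0.96 |
| 80% treated, 60% untreated | carry first | 0.05 + 0.0448 = 0.0948 | 0.10 + 0.0126 = 0.1126 | 0.83 |

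The first pair moves towards 1 and the second away from it. These are binary odds ratios, used only to show direction; the plan specifies a proportional odds model. In the first scenario the masked treated cases number 64 × 0.70 × 0.30 × 0.08 = 1.1.

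**4. D14.** Surveys at D21 and D28 postdate D14, so they cannot contradict a D14 value. With no earlier scale rating scheduled, the document also leaves open what would be carried to D14.

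**The case against.** The strongest reply is that the order is inferred. No sentence says that carrying forward precedes searching. The primary-endpoint list it points to cannot be a strict sequence either, because its censoring rules would dispose of nearly everyone before the survey is reached. The SAP, which is not shown, is to cover data manipulations and may settle precedence. This stands in part: the order follows from sentence sequence and from limiting the search to missing values, not from an explicit rule. But it is the natural reading, and on any reading nothing says what happens when a later record contradicts a carried value.

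A second reply is that the scale is clinician-rated, so a self-report is only a substitute source. That is fair. The protocol nevertheless accepts the survey as a recovery source, and a contemporaneous report bears on D28 more directly than a rating two weeks old.

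Several stronger readings are tempting and are not supported:
- That D14 values are distorted in the same way. Date order rules this out, and resolution or death before D14 can be known from dated records.
- That survey data are overwritten. They sit in a separate database and are bypassed, not altered.
- That the D28 scale is the only analysis able to show early recrudescence. D60 and D180 are assessment times, and nothing says earlier episodes are excluded.
- That the treatment odds ratio is pulled towards 1. The second scenario above shows the opposite.

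**Conclusion.** The point holds for D28. As the steps are written, a D14 rating of resolved fills a missing D28 rating and closes off the search of records that could contradict it. The D28 proportion resolved can therefore be overstated, by about 0.03 to 3.2 percentage points under the assumed ranges (0.8 points, about 5 of 601, in the middle case). It is zero if no affected participant has a contradicting record. The size rests wholly on assumed missingness, resolution, recrudescence and survey completion. No direction can be given for the treatment odds ratio. This is a modest fault in a secondary outcome of a mainly descriptive study. It is still worth correcting before analysis, because the rule as stated can assign a value that data already collected would show to be wrong.

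**What to change.** In the missing-data paragraph of Statistical method (and in the SAP), state the order for the four-level scale:

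1. Search medical notes, SAE records and the D21 and D28 surveys before any carrying forward.
2. Carry resolved to D28 only when no later record shows active lesions or a serious complication.
3. Always carry death.
4. As a clarification, derive a missing D14 level from dated resolution, SAE/hospitalisation and death records, since no earlier scale rating is scheduled.

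The cost is a few sentences and no new data collection. D28 resolution may look slightly less favourable, and some values will rest on self-report, so the number of values from each source should be reported. Participants enrolled retrospectively may have no survey to search. Where no contradicting record exists, resolved would still be carried and the reordering recovers nothing.

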## Oversight and monitoring

### Composition roles, and responsibilities of the coordinating centres, and trial study committee

**
*Overall study coordination.*
** University of Oxford, United Kingdom. Coordinating Centre (EU): ANRS|MIE; Coordinating Centre (Switzerland): Hôpitaux Universitaires de Genève; Coordination Centre (Singapore): Tan Tock Seng Hospital. Each coordinating centre is responsible for the management of the study in a specific country or region. The coordinating centres are responsible for arranging any study-specific agreements with the local participating sites. They also act as sub data processor and conduct on-site monitoring if necessary.

**
*Study Steering Committee (SSC).*
** The role of the SSC is to provide overall supervision for the study on behalf of the Sponsor and to ensure that the study is conducted according to the protocol and all relevant regulations and local policies.

The responsibilities of the SSC are:

To provide advice, through its Chair, to the Study Operations Committee (SOC) and the Sponsor on all aspects of the studyTo make suggestions for amendments and review and approve amendments to study documentation, including the study protocol, participant information sheets and case report forms (CRFs) provided by the SOCTo approve the statistical analysis planTo ensure that all relevant approvals are obtained before the study beginsTo monitor and supervise the progress of the study towards its overall objectives, review accrual and results of the study, adherence to the protocol, patient safety and the consideration of new information of relevance to the study and the research questionTo assess integrity and completeness of data collectedTo consider new information relevant to the study
*e.g.*, results from other studies that may have a bearing to the conduct of the study and deciding on appropriate actionTo provide input into the interpretation and writing up of the study resultsTo maintain confidentiality of any study information that is not in the public domainTo respond to study correspondence and any questions in a timely fashion

The MOSAIC Steering Committee is a multidisciplinary group who jointly have responsibility for the design, conduct and evaluation of the clinical research project.

**
*Study Operations Committee (SOC).*
** The role of the Operations Committee is to oversee the day-to-day management, conduct and progress of the study. Any issues identified by the Operations Committee are reported to the Steering Committee.

The responsibilities of the SOC are as follows:

To agree upon amendments to study documentation, including the study protocol, participant information sheets and case report forms (CRFs), and seek approval from the SSC before submissionTo finalise the statistical analysis plan for review by the SSCTo finalise standard operating procedures (SOPs), the study monitoring plan and data monitoring plan (SSC approval not required)To provide clinical or other expert guidance on study-based matters such as clinical and practical queries and interpretation of information recorded on CRFsTo oversee recruitment, address any issues with recruitment at study sites, and report any concerns to the SSCTo oversee study monitoring and address any issues raised during centralised monitoring, including making recommendations for on-site monitoring, and report any concerns to the SSCTo provide input into the interpretation and writing up of the study resultsTo maintain confidentiality of any study information that is not in the public domainTo respond to study correspondence and any questions in a timely fashion

The SOC should maintain confidentiality of all information it receives. Members should not discuss confidential issues from their involvement in the study until the primary results have been published.

The MOSAIC SOC is a multidisciplinary group who jointly have responsibility for the conduct of the clinical research project.

**
*The EU coordination Committee.*
** The role of the EU coordination Committee is to oversee the day-to-day management, conduct and progress of the study in the EU participating countries.

**
*Virology Task force.*
** The Virology task force group gathers virologists from the participating countries in the aim to share and harmonise virologic techniques for the study.

**
*Statistical analyses group.*
** The Statistical analyses group develops and designs the Statistical Analysis Plan.

(see ‘Additional File 2: Appendix H’ in
*Extended data* for Contributors’ names, roles and institutions)
^
7
^

### Composition of the data monitoring committee, its role and reporting structure

As this is not a randomised clinical trial, a data monitoring committee has not been convened. A medical monitor has instead been appointed to oversee issues related to participant safety.

The responsibilities of the medical monitor include, but are not limited to, commenting on any safety considerations related to the protocol, reviewing all Serious Adverse Event (SAE) reports and providing a causality assessment of the relationship between the event and tecovirimat and/or the study procedures, periodically reviewing a line listing of all AEs reported, reviewing all major protocol deviations, and providing advice on their management.

### Harms

**
*Safety reporting.*
** The assessment of safety outcomes—a study objective—requires adverse event reporting, serious adverse event reporting and collection of pregnancy outcomes in both treated and non-treated cohorts.

The study procedures carry minimal risk and therefore AE related to the study procedures are not anticipated.

AE and SAE data are collected in the eCRF from the date that the participant’s diagnostic sample for mpox infection was collected or the date of enrolment (whichever comes first) until D28.

*

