### Outcomes

**
*Primary outcome measure.*
** The primary outcome measure of this study is the participant’s time to lesion resolution without any serious complications. Lesion resolution is the first day on which all lesions are resorbed, scabbed or desquamated and mucosal ulcers healed. Lesion resolution is assessed until a maximum of 14 days since the date that the diagnostic sample is taken (for participants who do not receive mpox-specific antiviral treatment) or the day of treatment initiation (for participants who receive mpox-specific antiviral treatment).

**
*Secondary outcomes.*
** Secondary outcome measures evaluate clinical and virologic outcomes. Clinical outcomes are assessed on the basis of:

1. Clinical status on day 14 and day 28 according to a four-point ordinal scale assessed by a physician or a study nurse. The ordinal scale is a) all lesions are resolved and no serious complications, b) active lesions and no serious complications, c) serious complication and/or hospitalization due to mpox, or d) death.2. Evidence of recrudescence or relapse at day 60 and day 180.

*Note:* A "serious complication" is any complication associated with a Serious Advent Event (SAE) that is life-threatening, results in hospitalisation, prolongation of existing hospitalisation, disability, incapacity, or a congenital anomaly; or any other complication that is considered medically significant.

Virologic outcomes in Tier 1 are assessed on the basis of:

1. Change from baseline in mpox virus DNA levels in throat swabs on days 4, 8, 14 and 28.2. Change from baseline in mpox virus DNA levels in blood on days 4, 8, 14 and 28.3. Presence of mpox virus DNA in lesion swabs on days 4, 8, 14 and 28.

The study also assesses the number and type of SAEs, Suspected Adverse Reactions (SARS) and Suspected Unexpected Serious Adverse Reactions (SUSARs) within 28 days of enrolment.

Pregnancy outcomes defined as the final known health status of the mother and child are evaluated in any participants who are pregnant during the course of the study.

**
*Exploratory outcomes in Tier 2 and Tier 3.*
** Further virologic and immunological outcomes are also evaluated in France under this protocol to learn more about viral transmission, humoral and cellular immune responses. The outcome measures are as follows:

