### Participant timelime

Enrolment is the day that the informed consent form is signed, and the participant is enrolled in the study. Enrolment may be any day once the diagnostic sample is taken or after the patient has been considered a “presumptive case” by their treating clinician.

After enrolment, days are counted from the date the diagnostic sample is taken:

Day 1 is the date that the first sample to diagnose mpox was taken, regardless of when results became available. If the participant is enrolled on the same day that the diagnostic sample is taken, enrolment occurs on Day 1.If a participant is enrolled after the date that the diagnostic sample was taken, then study procedures start from the number of days since the sample was taken.

Participants who do not receive treatment follow the schedule from D1 and continue until D180. Participants who receive treatment immediately following diagnosis and enrolment in the study follow the schedule described above.

If a participant enters the study without receiving treatment and then begins receiving treatment at a later date, they initiate a new schedule of procedures by restarting at D1. This second D1 represents the date of treatment start. This extends the study participation period by the number of days between enrolment and treatment initiation.

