### Data collection methods

All data are recorded by the clinical and study teams directly on the REDCap (version 13.1.30)
^
9
^ electronic Case Report Form (eCRF) for each timepoint as defined in
Table 1.

**
*Demographics and medical history.*
** Data relating to the participant’s demographics and medical history are collected at baseline. Demographic includes sex at birth and ethnic group. Medical history includes data on comorbidities, results of pregnancy and HIV tests, data on signs and symptoms experienced by the participant between the collection of mpox diagnostic sample and the point of consent, and details of potential AEs and SAEs occurring between the collection of mpox diagnostic sample and the point of consent.

**
*Medical assessments.*
** Medical assessments are undertaken at baseline, and D14, 28, 60, and 180. These assessments can be conducted in person,
*via* video link or telephone. The data collected include the participant’s signs and symptoms, any treatment they may be receiving for mpox, AEs and SAEs details.

**
*Biologic sampling.*
** Baseline samples are the participant’s diagnostic samples that may have been collected under routine care before the participant signed the consent form. Blood* (~0.5ml to 20ml depending on local collection procedures), two lesion swabs and one throat swab are collected at D4*, 8*, 14, 21* and 28 where feasible to do so and permitted under local and national regulations–the asterisk (*) denotes procedures only for hospitalised subject; day 21 and 28 sampling only if day 14 sample is still positive.

Where local capacity limits sample collection, sites should prioritise the collection of D14 and 28 samples. All samples are tested by PCR only conducted in local laboratories in each participating country.

In Tier 2 in France, in addition to the sampling covered in Tier 1, additional samples of mucosa, saliva, anus, urine, semen or vaginal secretions, and blood are collected at baseline, D8, D14, D28, D60 (in case of oral, genital or anal lesion) and D180 (only if sample is positive at D60).

In Tier 3 in France, in addition to the sampling covered in Tier 1 and 2, additional samples of blood are collected at D28, D60 and D180.

Samples in Tier 2 and 3 are tested as in
Table 2.

**Table 2. T2:** Tests by sample type.

TIER	Test	Sample							
		Lesion	Throat	Mucosal lesion	Saliva	Anus	Blood	Urine	Semen or vagina secretion
1	PCR	X	X				X		
1&2	Bacterial STIs detection		X			X	X	X	

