Regarding virologic endpoints, the analysis will present the medians and interquartile ranges of mpox virus levels, measured in Cycle threshold (Ct) values, at different time points including baseline, and on days 4, 8, 14, and 28. These measurements will be used to assess viral clearance, categorized as a binary variable, in blood, skin lesions, and throat. The frequency of viral clearance will be reported based on the day of follow-up and treatment status groups.

Additionally, change in mpox virus DNA levels in throat and blood swabs will be compared to baseline on days 4, 8, 14, and 28 and will compared between treatment status using linear regressions at each timepoint.

Logistic regressions will model the presence of mpox virus DNA in lesion swabs at each timepoint.

Regarding safety endpoints, the number and type of SAEs, SARS and SUSARs within 28 days of enrolment will be described.

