Participants who encounter a SAR or SSAR, which are events deemed to be associated with the treatment, will be followed up until the event is resolved.

All SUSARs are reported to:

The EMA by the Sponsor’s Representative in the EU within seven days, if the event is fatal or life-threatening, or otherwise 15 days.The UK Research Ethics Committee (REC) within 15 days of becoming aware of the eventThe responsible ethics committee and SwissMedic in Switzerland within seven days, if the event is fatal, or within 15 days for all other events.
*Note:* All SAEs resulting in death are reported to the ethics committee and SwissMedic within seven days.The Domain Specific Review Board (DSRB) by the Sponsor’s Representative in Singapore within seven days.

In countries where the study is considered an observational study, it is the responsibility of the treating clinician to report (serious) AE directly to national and regional regulatory bodies according to applicable national and regional legislation i.e., the MHRA’s Yellow Card system in the UK.

Please see ‘Appendix G, Additional File 2’ in
*Extended data* for full details of the SAE reporting process for the study
^
7
^.

There may also be additional country specific requirements for safety reporting depending on regulatory requirements, in particular, the additional requirements for the EU/EEA are found in Appendix H, Additional File 2 “safety reporting for EU/EEA sites” section”.

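### Harms closes AE and SAE collection at D28, but other sections collect SAEs to D180, set no end date for SAE reporting, and count the safety outcome from enrolment

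*Protocol article*

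**What the plan says.** Five places in the protocol article bear on when SAEs are captured.

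- **Harms, safety reporting:** AE and SAE data go into the eCRF from the diagnostic sample or "the date of enrolment (whichever comes first) until D28".
- **Data collection methods, medical assessments:** "Medical assessments are undertaken at baseline, and D14, 28, 60, and 180". The data taken there include "any treatment they may be receiving for mpox, AEs and SAEs details", with no exception for the two late visits. Table 1 also marks the medical assessment at D60 and D180.
- **Harms, definition of SAEs:** sites report all SAEs to the sponsor within 24 hours of becoming aware of them. No end date is given. A separate rule covers serious and other adverse reactions, "which are events deemed to be associated with the treatment, will be followed up until the event is resolved".
- **Outcomes and Statistical methods:** the safety outcome covers "Suspected Unexpected Serious Adverse Reactions (SUSARs) within 28 days of enrolment", and the analysis repeats that "the number and type of SAEs, SARS and SUSARs within 28 days of enrolment will be described".
- **Participant timeline:** "Day 1 is the date that the first sample to diagnose mpox was taken". Enrolment may be later than that day, and a participant who starts treatment later restarts at a second D1. The Recruitment section adds that patients were enrolled retrospectively from January 2023.

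**The concern.** AEs and SAEs are a stated secondary objective, so the period over which they are captured should be the same at every site. As written, one section closes the record at D28, another keeps collecting at D60 and D180, and the reporting duty has no end. Two sites acting in good faith could hold different SAE records for identical patients, and a count of late SAEs would partly reflect which section each site followed.

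There is a second difficulty. The collection cut-off and the planned outcome both use the number 28 but count from different days. Whenever enrolment falls after D1, the outcome asks for SAEs on days that the Harms section leaves uncollected.

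**Working it through.** The plan states no figure to reproduce. The check sets the rules side by side and then counts days.

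**Step 1: one event under each rule.** Take an SAE that begins on D45 and comes to light at the D60 assessment.

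- Harms, safety reporting: collection closed at D28, so it is not recorded.
- Data collection methods and Table 1: SAE details are taken at D60, so it is recorded.
- SAE reporting rule: all SAEs are reported within 24 hours of awareness, so it is reported.
- Safety outcome: it counts only if D45 lies within 28 days of enrolment. With enrolment on day k as the first of the 28 days, this needs k ≤ 45 ≤ k + 27, so k from 18 to 45.

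The first rule conflicts with the second and third. The period in dispute is D29 to D180, which is 180 − 28 = 152 days.

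**Step 2: the planned outcome window against the D28 cut-off.** Inputs: D1 is the diagnostic sample (Participant timeline); collection ends at D28 (Harms); the outcome covers 28 days from enrolment (Outcomes, Statistical methods). For enrolment on day k the outcome window is Dk to D(k + 27).

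- Days inside the collection window: 28 − k + 1 = 29 − k for k ≤ 28, and 0 after that.
- Days after the cut-off: 28 − (29 − k) = k − 1 for k ≤ 28, and 28 after that.

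| Enrolment day k | Outcome window | Days collected under Harms | Days after the cut-off |
|---|---|---|---|
| 1 | D1–D28 | 28 | 0 |
| 8 | D8–D35 | 21 | 7 |
| 15 | D15–D42 | 14 | 14 |
| 29 | D29–D56 | 0 | 28 |

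The article gives no distribution of k, so these rows are illustrations. Retrospective enrolment makes values of 29 or more plausible. In that case the outcome, read literally, and the Harms collection window share no day.

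The table assumes that the 28 days run forward from enrolment and that the diagnostic-sample count applies. If enrolment is counted as day 0, one further day falls after the cut-off. For a participant who restarts at a second D1, the cut-off moves later if D28 is meant on the new schedule; the Harms section does not say which schedule it means.

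**The case against.** The strongest reply is that the Harms section sets the specific rule and the medical-assessment paragraph only lists form content for all visits. On that reading, the D60 and D180 forms update events that began by D28. The planned safety outcome is also limited to 28 days, so for a participant enrolled on D1 no planned safety analysis loses anything. The second part stands, and it limits the impact. The first is a possible reading, but nothing in the article says so, and the 24-hour duty for all SAEs points the other way. The appendix with the full SAE reporting process is cited but not shown. It may clarify practice, but it would not remove the conflict between the sections.

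A reader might also infer more than the article supports:

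- **That the serious-complication category of the four-point scale loses its basis after D28.** A serious complication "is any complication associated with a Serious Advent Event (SAE) that is life-threatening", among other criteria. However, that category also admits hospitalisation due to mpox, and the definition takes in other medically significant complications. The scale is a named outcome only at D14 and D28. At D60 and D180 the named outcome is recrudescence or relapse, which is not defined through an SAE.
- **That untreated participants have no planned follow-up of SAEs still open at D28.** Every participant has D60 and D180 assessments, and inpatients are assessed daily until discharge.
- **That treated and untreated groups cease to be comparable.** The follow-to-resolution rule separates events by attribution to treatment, not by group: an unrelated SAE in a treated participant is handled like one in an untreated participant.
- **That the 152 disputed days measure lost data.** They are calendar time and count no events.

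**Conclusion.** The contradiction is in the current text. Whether an SAE arising after D28 enters the study record depends on which section a site follows.

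The effect on the planned safety outcome is narrower. It is nil for enrolment on D1. For later enrolment, k − 1 days of the 28-day window fall beyond the collection cut-off, reaching all 28 when k is 29 or more. How many participants this affects, and how many SAEs fall in those days, cannot be derived from the article.

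The conclusion rests on reading D28 on the diagnostic-sample count and on reading the outcome window as running forward from enrolment. It does not rest on any claim about the four-point scale, untreated participants or group comparability.

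**What to change.** State one SAE collection window with one time origin, and use it in Outcomes, Data collection methods, Statistical methods, and both the collection and the reporting rules in Harms. Say which D1 applies when a participant restarts the schedule at treatment.

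One way that uses existing visits is to record SAEs at the D60 and D180 assessments, keep non-serious AEs to D28, and describe SAEs arising after the 28-day window separately from those within it. Limiting the medical-assessment paragraph to visits up to D28 would settle that conflict too, but it would leave the outcome window uncovered for late enrolment unless its origin were also changed to match. A new rule for following every open SAE to resolution is a matter of preference and is not needed to reconcile the text.

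The cost is a few more SAE records for sites and sponsor, plus a protocol amendment, which the article says needs ethics committee approval before implementation. Enrolment has stopped and the last visits are expected in January 2024, so some late visits may already be complete. The article allows the eCRF to be completed from existing medical notes, which gives a route to those data.
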